##### Diurnal clock gene assessment

Clock gene expression from oral cheek swabs will be used to assess peripheral circadian physiology at 8 weeks. Participants will be asked not to eat, drink, chew gum, or smoke within 60 min of each sample collection, and to rinse their mouth with water prior to collection. Participants will be provided with a ‘kit’ containing collection tubes in a foam rack, sterile buccal swabs, a cooler with blue ice packs, and an instruction sheet with a checklist. Participants will be asked to collect samples every 3 h, beginning 1 h after habitual wake time, for a total of 6 samples. Buccal mucosa samples will be collected by participants gently swabbing the inner cheek on both sides using a cytological brush (i.e., a buccal swab). After collection, participants will immediately place the oral mucosa samples into RNAlater reagent (Sigma-Aldrich, St. Louis, MO, USA) already contained in collection tubes. The cooler with samples will be collected by an experimenter from the participants’ homes and measured in the lab with real-time quantitative polymerase chain reaction.

##### Sleep and diurnal rhythm assessment via actigraphy and distal temperature

We will use the GENEActiv (Activinsights Inc.) wristband to record continuous activity counts and ambient light-exposure. Actigraphy data will be collected during baseline for two weeks and for 3 weeks at week 7. An integrated RGB light sensor records light measurements to help assess the impact of ambient light on human circadian and sleep physiology. The GENEActiv wristband is capable of a month of continuous recording and will not need to be recharged during the period of wear. The device is waterproof, allowing participants more freedom to wear the watch when completing normal activities. Actigraphy data are collected via an onboard 3-axis accelerometer and will be analyzed for sleep onset, offset, duration, and efficiency. Diurnal rhythm amplitude and stability will also be assessed using this activity data. Participants will be provided instructions and will not have access to data as it is collected on the device. Clocklab software (Actimetrics, Lafayette IN) will be used to calculate diurnal amplitude, mesor, and acrophase. Interdaily stability (IS), and intradaily variability (IV) will be calculated using non-parametric analyses in Clocklab. Sleep onset, offset, duration, and efficiency indices will be determined using validated algorithms from Activinights.

As a secondary measure of diurnal rhythmicity, we will use iButtons to record wrist temperature (temperature logged every 5 min). The iButton is a small (17.35 mm diameter × 5.89 mm depth) data logger that can be used to record human skin temperature at selected intervals and is regularly applied to studies of circadian rhythms and sleep/wake research (e.g., [123, 124]). iButtons will be used to chronically record wrist skin temperature when actigraphy measures are collected. The iButtons will be placed on the top of the wrist and secured in place with self-adherent cohesive wrap tape made of medical-grade non-woven, hypoallergenic fabric.

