##### Actigraphy and biological measures

For 10 days during baseline, participants will be asked to wear the Dexcom G6 continuous glucose monitor to provide 24-h continuous glucose levels, the GENEActiv wristband (Activinsights Inc.) to collect activity and sleep data, and a wrist-worn iButton to collect distal temperature. Participants will perform at home salivary collection for DLMO and inflammation assessment. They will be asked to collect 6 buccal cheek swabs (every 3 h) across the course of one day to assess peripheral clock gene expression. Participants will be asked to visit Quest Diagnostics for a comprehensive metabolic panel (CMP) and glucose tolerance test.

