##### Mid-intervention

Participants will be asked to complete 8 days of sleep diaries (core CSD). Participants will wear the Dexcom G6 CGM to collect glucose levels continuously for 2 weeks and wear the GENEActiv (Activinsights Inc.) wristband to collect activity/sleep data for 3 weeks. Participants will perform at home salivary collection for DLMO assessment and collect buccal cheek swabs to assess peripheral clock gene expression. Participants will visit Quest Diagnostics for a CMP and glucose tolerance test.

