***Potential Mechanisms of Change***							
Continuous glucose monitoring	HC		2 weeks	2 weeks starting week 7			
Actigraphy/Distal Temperature	HC		2 weeks	3 weeks starting week 7			
Metabolic Panel	QD		X	X			
Glucose Tolerance Test	QD		X	X			
DLMO	HC		X	X			
Clock Genes	HC		X	X			
Inflammation	HC		X	X			
Core Consensus Sleep Diary (CORE CSD)	SR		10 days	10 days			
PROMIS: Sleep Disturbance and Sleep-Related Impairment Scales	SR		X	X	X		X

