##### Continuous glucose monitoring

Continuous glucose monitoring will be conducted to examine daily patterns of glucose activity and their amplitude. Continuous glucose monitoring will be performed using the Dexcom, G6 CGM. Researchers will place the CGM onto the back of the upper arm of participants to ensure proper placement which will also activate the CGM. Participants will not have access to data while wearing the monitor. Participants will wear the G6 CGM monitor for 10 days at both baseline and week 6, before removing the sensor using instructions provided.

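### Wear lengths for actigraphy, wrist temperature and CGM contradict each other, and the longer actigraphy follow-up would lower interdaily stability with no true change if full records are scored

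*Protocol article*

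**What the plan says.** The protocol article gives wear lengths in four places.

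- **Baseline, actigraphy and wrist temperature.** The section on actigraphy and biological measures says "For 10 days during baseline, participants will be asked to wear the Dexcom G6 continuous glucose monitor", and the same sentence covers the wristband and the temperature logger. The measures section and Table 1 both give two weeks instead.
- **Follow-up, actigraphy and wrist temperature.** The Mid-intervention section has participants wearing the "wristband to collect activity/sleep data for 3 weeks". The measures section agrees ("Actigraphy data will be collected during baseline for two weeks and for 3 weeks at week 7"), as does Table 1. Temperature is logged whenever actigraphy is collected, so it follows the same windows.
- **CGM.** The baseline section gives 10 days and the Mid-intervention section two weeks ("Participants will wear the Dexcom G6 CGM to collect glucose levels continuously for 2 weeks and wear the GENEActiv (Activinsights Inc.) wristband"). The CGM section gives 10 days both times ("Participants will wear the G6 CGM monitor for 10 days at both baseline and week 6"). Table 1 gives two weeks both times, with follow-up entered as "2 weeks starting week 7".

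On scoring, the measures section says "Interdaily stability (IS), and intradaily variability (IV) will be calculated using non-parametric analyses in Clocklab". H5 uses change in sleep and in the amplitude of activity and temperature rhythms at week 8. The secondary analyses compare actigraphic sleep at 8 weeks with baseline.

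**The concern.** There are two problems.

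First, the schedule is inconsistent. Participants and staff need one instruction per device, and an analysis plan written later cannot settle how long a device was worn.

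Second, the actigraphy records are unequal whichever baseline figure is right: 10 or 14 days, against 21. Most rhythm indices tolerate this, but IS does not. It is the variance of the average 24-hour profile divided by the total variance. Averaging over few days leaves noise in the profile, and that noise counts as stability. A short baseline is therefore inflated more than a long follow-up, and IS drops between them even if nothing has changed. The trial expects TRE to improve rhythms, so the drop could hide a real gain in stability.

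**Working it through.** **Inputs from the article.** Record lengths of 10 or 14 days at baseline and 21 at follow-up; 125 analysable participants; two-tailed alpha of .05. The article gives no IS value, SD or bias, so there is no stated figure to reproduce.

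**Assumptions not in the article.** True IS of 0.3 to 0.7; SD of individual change in IS of 0.08 to 0.15.

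**Step 1, expected IS.** With D days, E[IS_D] ≈ IS + (1 − IS)/D. At true IS 0.5:

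- 10 days: 0.5 + 0.5/10 = 0.550
- 14 days: 0.5 + 0.5/14 = 0.536
- 21 days: 0.5 + 0.5/21 = 0.524

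**Step 2, spurious fall.** From D1 days at baseline to D2 at follow-up, the fall is (1 − IS)(1/D1 − 1/D2).

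- 14 to 21 days: 1/14 − 1/21 = 0.0238. The fall is 0.017 at IS 0.3, 0.012 at 0.5 and 0.007 at 0.7.
- 10 to 21 days: 1/10 − 1/21 = 0.0524. The fall is 0.037 at IS 0.3, 0.026 at 0.5 and 0.016 at 0.7.
- Equal lengths: the bracket is zero, and so is the expected artefact.

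**Step 3, simulation check.** Records were hourly, with a 24-hour cosine plus autocorrelated noise (lag-one correlation 0.5), 4,000 per setting. At true IS 0.5, mean IS was 0.543, 0.533 and 0.521 for 10, 14 and 21 days, so the falls were 0.023 (10 to 21) and 0.012 (14 to 21). Delaying free days by 1.5 h gave 0.532, 0.517 and 0.507, and falls of similar size.

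**Step 4, other indices in the same simulation, no free-day delay.** At true IS 0.5, from 14 to 21 days:

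- cosinor amplitude: 1.005 to 1.003
- intradaily variability: 0.539 to 0.538
- relative amplitude: 0.294 to 0.291

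All move by less than 1%. At true IS 0.3, from 10 to 21 days, amplitude moves about 1% (1.018 to 1.008) and relative amplitude about 4% (0.307 to 0.296).

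**Step 5, effect on a mean comparison.** Suppose mean IS change were tested with a paired t-test in 125 people. At true IS 0.5 and SD of change 0.10, the standardised shift is 0.0119/0.10 = 0.119 for 14 versus 21 days, and the chance of a significant result with no true change is about 26%. For 10 versus 21 days it is 0.262 and about 83%. Over true IS 0.4 to 0.6 and SD 0.15 down to 0.08, the chance is 11% to 51% and 34% to 99% respectively, against a nominal 5%.

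**Step 6, weekend mix.** Any 14 days contain 4 weekend days and any 21 contain 6, which is 28.6% in both. Ten days contain 2, 3 or 4 depending on start day (20% to 40%). Over the seven start days the counts sum to 20, and 20/70 = 28.6%, so the average imbalance is zero. If free-day sleep is assumed 1.5 h later, one person's mean sleep midpoint could shift by (0.20 − 0.286) × 90 ≈ −8 min to (0.40 − 0.286) × 90 ≈ +10 min. That is start-day noise, not bias.

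**The case against.** The strongest reply is that recording more days than are scored is no error. The article sets its comparison at week 8, which may mean a window within the three-week record, and valid-day and truncation rules are commonly left to the full protocol or analysis plan. This stands: the IS artefact is conditional on scoring full records, which the article neither states nor rules out. It does not answer the contradictory wear lengths.

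A reader might infer more than the text supports:

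- **That the planned rhythm analyses are generally distorted.** No hypothesis names IS. H5 names sleep and amplitude, the ambulatory aim names relative amplitude, and these hardly move or move little.
- **That the adherence paths are biased.** For fixed lengths the bias is a near-linear rescaling, (1 − 1/D)·IS + 1/D. In baseline-adjusted structural equation paths most of it goes into intercept and scale. Contamination would need valid wear days to vary with adherence, on which the article gives no data.
- **That CGM records are unequal by design.** Only one pairing of passages gives 10 days then two weeks; two other places give equal lengths. This is a contradiction to reconcile, and no CGM artefact was computed.
- **That the weekend mix biases sleep timing.** It has no effect at 14 versus 21 days and averages to zero at 10 days.

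**Conclusion.** The contradictions are established from the text: two baseline lengths for actigraphy and temperature, three versions of CGM wear, and CGM follow-up placed either at week 6 or from week 7.

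The measurement consequence is real but narrow. If IS is scored from full records, its mean falls by about 0.01 to 0.02 (14 versus 21 days) or 0.02 to 0.04 (10 versus 21 days) with no true change, for an assumed true IS of 0.7 to 0.3. The direction is against TRE, so it cannot produce a false benefit in stability. It matters for a mean pre-post comparison of IS; how often that would mislead depends on an SD of change that the article does not give. The primary mediator, clock-gene amplitude, does not use these records. Severity is minor, on secondary measures.

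**What to change.** 1. State one wear length and one follow-up timing per device, and make the baseline, Mid-intervention, actigraphy and CGM sections and Table 1 agree.
2. Compute IS, and for consistency the other actigraphy and temperature indices, from the same number of consecutive valid days at both time points, with the follow-up window placed around week 8.
3. If the 10-day baseline stands, also match the number of free days. The article already secures at least two free days for the sleep diary and mood probes.
4. Use the full follow-up record only as a sensitivity analysis.

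The cost is protocol wording and one truncation step in scoring. Follow-up estimates become slightly noisier because fewer of the 21 days are used.

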##### Dim Light Melatonin Onset (DLMO)

Prior to collection, a COVID screening questionnaire (see attachments) will be administered. Sample collection will not commence if any response is in the affirmative. To assess central circadian timing, DLMO will be examined during the baseline period and at week 8. While historically conducted in a laboratory setting, home collection of DLMO has been validated (e.g., [125, 126]). Prior to collection, an experimenter will perform a home visit to determine the best location to collect samples based on ambient lighting. If needed, blackout curtains will be provided. To ensure dim lighting requirements are adhered to, participants will use the MiEye Wearable Light Sensor (Circadian Health Innovations, Australia). A demonstration of how to collect a saliva sample will be given, and participants will receive a home saliva collection kit. Participants will be instructed not to consume any alcohol or caffeine at least 24 h before each home phase assessment. Participants will be instructed to prepare food ahead of time so they can eat between the hourly saliva samples at home if desired.

The home saliva collection kit consists of an insulated cooler with removable ice pack, a paper checklist with space to report any atypical events, a tube rack, collection tubes, and a soft toothbrush. Participants will also be offered battery-powered tea candles to assist in ambient lighting in the collection area, bathrooms, and any other rooms in which visits might occur during collection. Participants will be instructed to follow the checklist whenever alarms sound on the timer, and to check off events when completed.

A phone alarm will occur 30 min before the first saliva sample to remind participants to ensure provided blackout curtains are placed. Participants are asked to brush their teeth with the provided toothbrush if they have eaten any food, rinse with water, and remain seated until after the next saliva sample. At the time when a saliva sample is to be collected, the checklist prompts participants to open the first labeled collection tube and use a passive drool approach to collect around 1 ml of saliva. Participants will collect samples hourly beginning 5 h before their habitual bedtime until 1 h after their habitual bedtime. Samples will be placed into the freezer at the end of collection and samples and kits will be collected at a time scheduled by the participant.

To supplement our primary indices of circadian function, we will examine changes in sleep (the gold standard CORE CSD measures of quality of sleep and reduced variability in sleep midpoint, along with PROMIS sleep disturbance and sleep-related impairment, and actigraphy and temperature measures). To assess whether the sleep and light guidance offered as part of the TRE intervention leads to improved sleep hygiene, we will gather the Sleep Household Environment and In-Bed Behaviors [92].

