#### Hypotheses

To examine the mechanisms through which TRE leads to symptom improvements, we will investigate a battery of biological measures at baseline and 8 weeks. We predict that TRE adherence will lead to a change in the amplitudes of diurnal clock gene expression and diurnal phase (DLMO) at 8 weeks, which will lead to a cascade of change in symptoms (mania and depression at week 10, and then a downstream change in QOL at 16 weeks).

H1: TRE adherence will predict changes in diurnal amplitude of clock gene expression from baseline to week 8.H2: The degree of change in diurnal amplitude of clock gene expression (at week 8) will be associated with the degree of improvement in symptoms (week 10), controlling for change in glucose tolerance and inflammation (week 8) and for baseline levels of diurnal amplitude, symptoms, glucose tolerance, and inflammation.H3: There will be an indirect effect of TRE adherence on QoL through symptoms.

Ambulatory data will provide opportunity for lagged tests of how biological rhythmicity improvements (actigraphy RA) promote improved sleep, resulting in diminished mood variability (ecological momentary assessment; EMA Mood Zoom) [74].

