### Inclusion/exclusion criteria

The inclusion/exclusion criteria are designed to maximize participant safety and the applicability of TRE, and secondarily, to maximize the generalizability of the findings. We will recruit adults aged 18–65 years who meet diagnostic criteria for bipolar I disorder or bipolar II disorder per the Diagnostic Interview for Anxiety, Mood, and OCD and Related Neuropsychiatric Disorders (DIAMOND), but not cyclothymia, BD not otherwise specified, or BD due to another medical condition.

To maximize the ability to determine whether TRE improves sleep- or circadian-related outcomes, the entrance criteria will include at least some current sleep or circadian sleep–wake concerns. We do not expect this to greatly diminish generalizability, as more than 75% of those with BD report sleep or circadian concerns [77]. This inclusion criteria will be met by any one of the following:

Score of ≥ 8 reflective of subsyndromal insomnia on the Insomnia Severity Index (ISI; [78–80])Early chronotype (midpoint of sleep on free days < 4.16 h) or late chronotype (midpoint of sleep on free days > 4.53) on the MCTQDisrupted social activity rhythms, as indicated by a score ≥ 30 on the Brief Social Rhythm Scale (BSRS) [81]Sleep (insomnia, hypersomnolence) or circadian sleep–wake (delayed phase, advanced phase, irregular sleep–wake, non-24-h sleep–wake-type) disorder diagnoses on the Structured Clinical Interview for Sleep Disorders-Revised (SCISD-R; [82]).

Other inclusion criteria include the following:English language adequate for completion of questionnaires or interviews, as indicated by speaking English for at least 10 years, speaking English at home, or proficiency as observed during the screening interview.Receiving medical care for BD (referrals will be provided for those who would like to begin care)Mood-stabilizing medication regimens need to be stable for at least one month. Those with BD II per the DIAMOND will be permitted to engage in the trial if not taking mood-stabilizing medication, as long as their provider has supported this treatment plan and continues to see them at least once every 3 months.Currently eating ≥ 12 h per day at least twice per weekAble to operate the camera function and respond to surveys by smartphone (loaner phones will be provided as needed)

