#### Potential moderators

We will gather several variables to assess their role in moderating outcomes. These include data on the types of psychotropic and sleep medicines, doses, and adherence levels at each self-report assessment to calculate summary scores for each major receptor type. At baseline, we will gather data on the Positive Urgency Scale [128], food insecurity (HFSSM; [94, 129]), and Menopause QoL sleep items [96, 97], as potential predictors of intervention outcome. At baseline and at 6 weeks, we will gather a Food Frequency Questionnaire to assess inadvertent changes in dietary intake (e.g., less dessert consumption after participants stop midnight snacks).

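### Home DLMO collection sets no rule for melatonin and describes no dose time on the sampling night, so in some users the measured onset can reflect the dose and not circadian phase

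*Protocol article*

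**What the plan says.** The Hypotheses section of the protocol article predicts that "TRE adherence will lead to a change in the amplitudes of diurnal clock gene expression and diurnal phase (DLMO) at 8 weeks". The section on DLMO states that "DLMO will be examined during the baseline period and at week 8" and gives the sampling grid: "Participants will collect samples hourly beginning 5 h before their habitual bedtime until 1 h after their habitual bedtime".

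That section describes the preparation closely. Light is controlled ("To ensure dim lighting requirements are adhered to, participants will use the MiEye Wearable Light Sensor"), and so are mouth residue and posture: participants are to "brush their teeth with the provided toothbrush if they have eaten any food, rinse with water, and remain seated". Among ingested substances, the instruction is "Participants will be instructed not to consume any alcohol or caffeine at least 24 h before each home phase assessment". A paper checklist leaves room for unusual events.

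The medication rules are in Inclusion/exclusion criteria. The stability rule reads "Mood-stabilizing medication regimens need to be stable for at least one month". The list of excluded medicines names no melatonin, melatonin agonist or hypnotic. Sleep-medicine use is nevertheless expected, because Potential moderators plans to collect it: "These include data on the types of psychotropic and sleep medicines, doses, and adherence levels at each self-report assessment". In Table 1 this record (the Somatotherapy row) is marked at baseline and in the week 8 column, the same two columns in which DLMO is marked.

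**The concern.** DLMO is the time at which salivary melatonin rises, and swallowed melatonin can also raise the assayed concentration. The trial selects people with insomnia symptoms, an early or late chronotype, irregular social rhythms, or a sleep or circadian diagnosis, so some melatonin use is foreseeable. An evening dose falls within the sampling window. If it precedes the participant's own rise, the first raised sample marks the dose.

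Two consequences follow for the change from baseline to week 8. Steady use at a fixed time holds the reading still and attenuates a true shift. Starting, stopping or re-timing a dose between the two nights can create a shift or hide one. The trial has a single arm (Trial design), so no control group would show the same artefact and let it be subtracted.

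A habitual nightly dose is not an unusual event, so the free space on the checklist would not reliably capture it.

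**Working it through.** The plan states no figure on this point, so there is none to reproduce. The check applies the article's own sampling grid.

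**Inputs from the article.** Samples are hourly from −5 h to +1 h around habitual bedtime: −5, −4, −3, −2, −1, 0, +1, which is 7 samples. There are two collections, baseline and week 8. Analyses are planned on 125 participants (Statistical analysis plan).

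**Assumptions, not in the article.** A sample taken at the moment of the dose is still unaffected, and the next hourly sample is raised. Onset is read at the first raised sample. Habitual bedtime is the same on both nights.

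**Step 1: reading on one night.** Measured onset = the earlier of (true onset, first sample after the dose). False advance = true onset − measured onset. Times are hours relative to bedtime.

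| True onset | Dose at −3 | Dose at −2 | Dose at −1 |
|---|---|---|---|
| +1 | reads −2, advance 3 h | reads −1, advance 2 h | reads 0, advance 1 h |
| 0 | reads −2, advance 2 h | reads −1, advance 1 h | reads 0, advance 0 h |
| −1 | reads −2, advance 1 h | reads −1, advance 0 h | reads −1, advance 0 h |
| −2 or earlier | no effect | no effect | no effect |

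The error therefore needs a late true onset together with a dose taken well before it.

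**Step 2: change between the two nights.** Change read = week 8 reading − baseline reading.

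- *False shift.* True onset at 0 on both nights, dose at −3 on the week 8 night only: −2 − 0 = −2 h, although nothing changed. With the dose on the baseline night only: 0 − (−2) = +2 h.
- *Hidden shift.* True onset moves from 0 to −1, dose at −2 on the baseline night only: baseline reads −1, week 8 reads −1, change 0 h.
- *Steady use.* True onset moves from +1 to 0, dose at −3 on both nights: both read −2, change 0 h against a true change of −1 h.

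**Step 3: effect of steady use on the group mean.** If a share p is masked on both nights with an unchanged dose time, and the true shift is the same in masked and unmasked participants, the mean shift read is (1 − p) × true mean shift. For illustration only:

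| Assumed p | Participants of 125 | True mean shift retained |
|---|---|---|
| 5% | 125 × 0.05 ≈ 6 | 95% |
| 10% | 125 × 0.10 ≈ 13 | 90% |
| 20% | 125 × 0.20 = 25 | 80% |
| 30% | 125 × 0.30 ≈ 38 | 70% |
| 40% | 125 × 0.40 = 50 | 60% |

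Here p is the share actually masked, which is smaller than the share taking melatonin, because Step 1 shows that many users would be unaffected.

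**The case against.** **The article is condensed.** It mentions a home visit, a demonstration, a checklist and attachments without reproducing them, so a medicine-time line may exist, and scoring rules may stand in an analysis plan that is not shown. This stands in part: the text cannot prove that dose time goes unrecorded. But the article chose to state the substance rule, the excluded medicines and the stability rule in detail. Followed as written, these leave out the substance being assayed.

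**Users can be identified.** A reader might infer that contaminated profiles could never be traced. The documents do not support that. The medication record falls in the same two Table 1 columns as DLMO, so if it captures melatonin, users can be flagged and starting, stopping or dose changes seen. What it is not described as giving is whether and when a dose was taken on the sampling night.

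**Only melatonin is at issue.** A reader might extend the argument to every sleep medicine. Other sleep medicines would not appear as melatonin in saliva. They could at most be an uncontrolled influence on sleep or phase. Nor does the article say that melatonin is permitted; that is inferred from the absence of any exclusion.

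**The size is easily overstated.** One could multiply an assumed user share by a 2 h error: 0.10 × 2 h = 0.2 h (12 min), or 0.30 × 2 h = 0.6 h (36 min). That requires every user to have a late onset, to dose early enough for a full 2 h error, and to be affected on one night only. These figures are near a worst case on a prevalence the documents do not give.

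**The consequence is limited.** DLMO is in the opening prediction but not in the wording of H1 to H6. The structural equation models use a latent variable for clock-gene amplitude, measured from cheek swabs, and the power calculation does not involve DLMO. This stands in full.

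**Conclusion.** The point holds for melatonin and for the DLMO phase measure only. As written, the procedure lets a melatonin dose taken before the participant's own rise be scored as circadian phase, and no dose time is described that would reveal it. In an affected profile with a true onset at bedtime, the false advance is 0 to 2 h for doses 1 to 3 h before bedtime. Where the true onset is 2 h or more before bedtime, a dose at −3 h or later has no effect on the onset read. These sizes rest on the hourly grid and on the reading rule assumed above. The number of participants affected is unknown.

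It would be wrong to infer that the trial's main conclusions are at risk: H1 to H3, the clock-gene mediator and the stated power are untouched. The point is still worth acting on, because the article names the DLMO change as a prediction and calls DLMO the standard measure of phase (Project aims), and because a dose time not noted on the night cannot be reliably recovered later.

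**What to change.** - **Record.** Add one line to the saliva checklist, at baseline and at week 8, for the product and clock time of any melatonin taken in the 24 h before and during sampling.
- **Score.** Prespecify that only samples collected before the dose are used, and that DLMO is set to missing if no onset has occurred by then. The rule should also say how a dose from the previous night is handled: one taken at habitual bedtime lies 24 − 5 = 19 h before the first sample and so falls within the recorded period.
- **Sensitivity analysis.** Use the medication record already planned (Potential moderators; Somatotherapy row of Table 1) to repeat the phase analysis without participants whose melatonin or other sleep medicine changed between the two collections.

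The cost is one checklist line and an analysis rule. The downside is that some DLMO values become missing, mainly in users with late onsets, so the number lost should be reported. No change to anyone's treatment is proposed.
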